#### Equipment required

The leg ergometer used in this trial is designed for supine and seated exercise, allowing safe application in early post-operative cardiac patients where standard cycle ergometry is unsuitable.

Its compact design, adjustable resistance, and ease of bedside positioning make it particularly useful for intensive care and Phase I cardiac rehabilitation settings [17].

#### Instrument description

Device: Portable Pedal Ergometer

Model: MediCycle-LCE

Manufacturer: Mediverse Healthcare Pvt Ltd, India

Type: Manual leg cycle ergometer, usable in supine or sitting positions

Features: Non-slip pedals with adjustable foot straps, digital display (time, RPM, distance), manual resistance knob (0–5 levels)

Reliability & Reproducibility: Demonstrated ICC >0.85 for repeated use in ICU/early cardiac rehabilitation settings [10, 13]

Administrability: Compact, safe for bedside use, suitable for both semi-recumbent and seated patients

All ergometer sessions will be supervised by trained physiotherapists, ensuring standardized resistance progression and patient safety during use.

#### Outcome measures

All outcomes will be assessed at two time points: baseline (post-operative day 1–2, before intervention) and at the end of the 10-day Phase I rehabilitation period (post-operative day 10). Assessments will be conducted by blinded physiotherapists in the hospital setting.

This trial has two co-primary outcomes: (1) scar healing measured by the Vancouver Scar Scale and (2) functional capacity measured by the 6-Minute Walk Test. Secondary outcomes include muscle strength (MMT) and quality of life (PHQ-9).

#### Primary outcome measures

Scar Healing (Vancouver Scar Scale): The Vancouver Scar Scale assesses four scar parameters—height, pliability, pigmentation, and vascularity—each scored to yield a total of 0–13, where higher scores indicate greater impairment. It is one of the earliest validated clinical tools for objective evaluation of post-surgical scars and is sensitive to short-term healing responses in hospital settings.Functional Capacity (6-Minute Walk Test): The 6MWT is a standardized sub-maximal exercise test that evaluates aerobic capacity and endurance. The total distance walked in six minutes reflects overall cardiopulmonary fitness. It is widely recommended in cardiac rehabilitation guidelines (AHA/ESC) for assessing early functional gains in post-CABG patients

#### Secondary outcome measures

Quality of life-PHQ-9: The Patient Health Questionnaire-9 (PHQ-9) is a validated screening tool for depressive symptoms. Scores of 5–9, 10–14, 15–19, and ≥20 indicate mild, moderate, moderately severe, and severe depression, respectively. This measure captures the psychological dimension of recovery, which can influence engagement and adherence during early rehabilitation.Manual muscle testing: Manual Muscle Testing assesses voluntary muscle strength against graded resistance (Grades 0–5). The examiner stabilizes the limb and applies resistance to determine maximal effort. It provides a practical, reproducible assessment of lower-limb strength when instrument-based testing is not feasible in post-surgical patients.

Together, these outcome measures represent the biopsychosocial recovery model, capturing scar healing (tissue integrity), functional performance (6MWT), muscular strength (MMT), and emotional well-being (PHQ-9). The chosen tools are particularly suitable for short-term, hospital-based Phase I cardiac rehabilitation and have established validity and reliability in this population.

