**Aim:**

To determine the relative benefits of leg cycle ergometry training for CABG patients with saphenous vein graft in phase 1 in terms of scar healing, muscle strength, functional ability, and quality of life.

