**Objectives:**

To evaluate the comparative efficacy of leg cycle ergometry exercise versus conventional physiotherapy on scar healing, muscle strength, functional capacity, and quality of life in CABG subjects with saphenous vein grafts during Phase I rehabilitation.

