**Methods:**

A randomized controlled trial will be conducted at Shalini Tai Meghe Super Speciality Centre with 70 CABG patients aged 45–65 years. Participants will be randomly allocated to Group A (conventional physiotherapy) and Group B (leg cycle ergometry with physiotherapy) for a 10-day intervention. Outcome measures include the Vancouver Scar Scale, Manual Muscle Testing, 6-Minute Walk Test, and Patient Health Questionnaire-9 (PHQ-9). Data will be analysed using the Mann-Whitney U test and the Wilcoxon signed-rank test; p<0.05 was deemed statistically significant.

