**Results:**

As this is a study protocol, no results are available yet. It is hypothesized that leg cycle ergometry, when added to conventional physiotherapy, will lead to greater improvements in scar healing, lower limb strength, functional capacity, and short-term quality of life during Phase I cardiac rehabilitation following CABG surgery.

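### Quality of life is a named objective, but its only instrument is the PHQ-9, which the protocol itself defines as a depression screen; the outcome label is broader than what is measured

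*Protocol article*

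**What the plan says.** Quality of life runs through the statements of purpose in the protocol article. The Abstract's Aim frames the comparison "in terms of scar healing, muscle strength, functional ability, and quality of life". The Objectives evaluate efficacy "on scar healing, muscle strength, functional capacity, and quality of life in CABG subjects with saphenous vein grafts during Phase I rehabilitation". The hypothesis, printed under the Abstract's Results heading, is that adding ergometry "will lead to greater improvements in scar healing, lower limb strength, functional capacity, and short-term quality of life". The Introduction repeats the same aim. The Sample size calculation also counts quality of life among the primary outcomes.

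The measurement side is narrower. The Abstract's Methods give the instruments: "Outcome measures include the Vancouver Scar Scale, Manual Muscle Testing, 6-Minute Walk Test, and Patient Health Questionnaire-9 (PHQ-9". The Outcome measures section names the two co-primary outcomes (scar healing and walking distance) and continues: "Secondary outcomes include muscle strength (MMT) and quality of life (PHQ-9". The entry under Secondary outcome measures is headed as quality of life, but its first sentence reads: "The Patient Health Questionnaire-9 (PHQ-9) is a validated screening tool for depressive symptoms". The score thresholds that follow are grades of depression, from mild to severe.

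**The concern.** An outcome label fixes what may be concluded from the result. Here the label (quality of life) and the definition (a depression screen) name different constructs, and the definition is the narrower one. If the report follows the label, a lower PHQ-9 score in the ergometry group could be presented as better quality of life, and a null result as no effect on it. Neither statement follows from a depression score.

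The condensed form of a journal article does not explain this. The article states both the label and the definition, and they disagree. A separate analysis plan could specify how the PHQ-9 is analysed, but it could not change what the PHQ-9 measures.

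**Working it through.** No arithmetic applies. The mismatch is one of construct, and no change in sample size, alpha or power would resolve it. The check is to set the relevant places side by side.

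**Step 1: where quality of life is promised.** It appears in the Abstract's Aim, Objectives and hypothesis, in the aim restated in the Introduction, under Outcome measures, in the item heading under Secondary outcome measures, and in the Sample size calculation.

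**Step 2: which instrument could measure it.** The article lists four instruments, and the list is the same in the Abstract, the Introduction and the Discussion.

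| Instrument | Construct according to the article |
|---|---|
| Vancouver Scar Scale | scar healing |
| 6-Minute Walk Test | functional capacity |
| Manual Muscle Testing | lower-limb strength |
| PHQ-9 | labelled quality of life; defined as a depression screen |

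Only the PHQ-9 is assigned to quality of life.

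**Step 3: how the article describes the PHQ-9.** Three descriptions go with one score:

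- Outcome measures, and the item heading under Secondary outcome measures: quality of life.
- First sentences of the item under Secondary outcome measures: depressive symptoms, with depression-severity bands.
- Closing text of Secondary outcome measures, and the Discussion: emotional or psychological well-being.

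The first is a label only. The second and third are the places where the article explains what the score captures, and both are narrower than quality of life. No section says that the PHQ-9 covers the physical, functional or social parts of quality of life, and no section limits the objective to its psychological part.

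**Step 4: whether the stated rationale closes the gap.** The Introduction acknowledges SF-36 and EQ-5D and prefers the chosen measures because they respond to short-term change in Phase I. That is a claim about responsiveness. A measure can respond well to change and still measure something other than the construct named.

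**Step 5: standing of the outcome.** Outcome measures makes it secondary. The Sample size calculation groups quality of life with scar healing and functional capacity as a primary outcome. The two sections conflict, so relabelling alone would leave depressive symptoms listed there as a primary outcome.

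**The case against.** The strongest reply is that the authors already treat the PHQ-9 as a psychological measure. Secondary outcome measures and the Discussion speak of emotional or psychological well-being. Blinding lists the assessed domain as psychological outcomes. The passage in the Discussion on what a positive trial would lead to speaks of physical, graft-site and psychological benefit, and does not mention quality of life. The choice of instrument is disclosed with a reason, the outcome is secondary, and PHQ-9 data remain fully interpretable.

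Much of this stands. A reader might infer that a PHQ-9 difference is bound to be reported as a quality-of-life benefit. The documents do not support that: the aim, objectives and hypothesis make such reporting possible, while other sections point to the narrower reading. A reader might also infer that SF-36 or EQ-5D should have been used. That would be a preference about instruments, and only the label is open to criticism here.

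The reply does not remove the contradiction. The narrower descriptions sit in the explanatory text. The sections that define what the trial sets out to show, and what it hypothesises, still say quality of life without qualification.

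**Conclusion.** The point holds as a labelling error in a secondary outcome. A PHQ-9 result from this trial can support a conclusion about depressive symptoms, which are one psychological aspect related to quality of life. It cannot support an unqualified quality-of-life conclusion.

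Two stronger readings are tempting. One is that the trial can say nothing that bears on quality of life; this goes too far, because the depression result stands and is relevant. The other is to count one of the four named domains as lost and quote that as a magnitude. The count treats a secondary outcome as equal to the two co-primary ones and measures no bias, power or error rate.

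The conclusion rests on the article's own definition of the PHQ-9 and on its instrument list being complete. The list is the same wherever it is given.

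**What to change.** 1. Relabel the outcome as depressive symptoms (PHQ-9 total score, at baseline on post-operative day 1–2 and at the end of the 10-day programme). Apply this in the Abstract's Aim, Objectives and hypothesis, in the Introduction's aim, and under Outcome measures and Secondary outcome measures.
2. Remove quality of life from the primary outcomes named in the Sample size calculation, without putting depressive symptoms in its place, because Outcome measures makes it secondary.
3. State that no quality-of-life conclusion will be drawn from the PHQ-9.

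When the time points are written out, the article's own schedule needs reconciling. Outcome measures puts the final assessment at post-operative day 10, while Data collection method runs the programme over days 2–11.

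The cost is wording and a recorded amendment; Trial status shows version 1.0 with none so far. The trial gives up a quality-of-life claim. The co-primary outcomes, the data collected and the tests are unaffected. Recruitment began in June 2025, so the change is best made before any analysis, when it cannot be taken for a label chosen after seeing the results.

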## Discussion

Coronary artery bypass grafting remains one of the most performed and effective revascularization procedures, yet donor-site complications from saphenous vein harvesting such as edema, pain and delayed scar healing can significantly restrict early mobility and delay recovery. Early rehabilitation and mobilization are vital to reduce postoperative functional decline and improve hospital outcomes. Leg cycle ergometry, a closed chain rhythmic exercise, can enhance venous return, improve peripheral circulation, and maintain muscle activation without imposing excess cardiac stress. Incorporating LCE during Phase I cardiac rehabilitation may therefore promote graft site healing, preserve lower limb strength and accelerate functional independence. The selected outcome measures—Vancouver Scar Scale (VSS), 6-Minute Walk Test (6MWT), Manual Muscle Testing (MMT), and PHQ-9—collectively capture the multidimensional nature of recovery. VSS evaluates donor site tissue integrity, 6MWT and MMT reflect physiological and functional capacity, while PHQ-9 captures short-term psychological well-being that influences adherence to rehabilitation. Earlier studies, such as those by Hirschhorn et al. [13] and Hamid et al. [10], demonstrated the safety and feasibility of early ergometry in CABG patients but did not assess localized donor-site outcomes or psychological domains. Hence, this trial addresses an important evidence gap by integrating lower-limb-specific intervention and comprehensive outcome evaluation within the early post-CABG recovery phase, especially in an Indian tertiary-care setting where structured Phase I cardiac rehabilitation is still developing.

This study’s strengths lie in its randomized, assessor-blinded design, use of standardized intervention checklists, and continuous safety monitoring to ensure patient protection and methodological rigor. However, limitations such as the single-center setting, small sample size, and 10-day intervention period may restrict generalizability and long-term interpretation. The inability to blind participants and therapists is inherent to exercise trials, but potential bias will be minimized through blinded assessors, uniform exercise protocols, and inter-rater reliability training. Despite these limitations, the study provides a feasible, cost-effective rehabilitation model that can be readily implemented in resource-limited cardiac units. If the findings confirm the hypothesized benefits, leg cycle ergometry could be incorporated as a routine component of early Phase I cardiac rehabilitation to enhance physical recovery, graft-site healing, and psychological outcomes. Future multicentre trials with extended follow-up are warranted to validate durability of effects and to establish broader clinical applicability. By establishing early-phase evidence from an Indian tertiary-care center, this trial contributes to the growing global focus on context-specific, low-cost cardiac rehabilitation models that address both physiological and psychosocial recovery. Future multicenter trials with extended follow-up are warranted to validate the durability and generalizability of these findings.

### Recruitment

Subjects will be recruited through the Cardiovascular and Thoracic Surgery (CVTS) Intensive Care Unit and Ward, Shalini Tai Meghe Super speciality Centre, Sawangi (Meghe), Wardha, Maharashtra, India. Enrollment into the trial and baseline assessments will occur prior to the initiation of intervention. Eligible patients meeting the inclusion criteria will be approached within 24–48 hours of achieving hemodynamic stability following coronary artery bypass grafting. The purpose, procedures, potential benefits, and risks of the study will be clearly explained, and written informed consent will be obtained from all participants prior to recruitment.

Recruitment will continue until the required sample size of 84 participants (42 per group) has been achieved. The schedule of enrollment, intervention, and assessments is presented in Fig. 2.

**Fig. 2 Fig2:**
[figure not shown]
SPIRIT Schedule of enrollment, intervention, and outcome measures

### Randomization

#### Sequence generation

Participants will be randomized in a 1:1 ratio to either the experimental or control group using computer-generated block randomization created by an independent statistician not involved in patient enrollment or assessment.

#### Allocation Concealment Mechanisms

Allocation will be concealed using the sequentially numbered, opaque, sealed envelopes (SNOSE) method. Physiotherapist will label and store the envelopes securely. Upon subject enrollment, the next envelope in sequence will be opened to reveal group allocation. This ensures allocation concealment and prevents selection bias.

#### Implementation

The allocation sequence will be generated by the biostatistician, while participant enrollment will be performed by the primary investigator. Group assignment will be carried out by the therapist after eligibility confirmation. The physiotherapists responsible for delivering interventions will not have access to the randomization list.

#### Blinding

Due to the nature of the intervention, participant and therapist blinding is not feasible because subjects will know whether they are performing leg cycle ergometry. However, outcome assessors (evaluating scar healing, muscle strength, functional capacity, and psychological outcomes) and data analysts will remain blinded to group allocation to minimize measurement and analysis bias.

To ensure assessor reliability, standardized training and checklists will be used for all outcome measures.

### Data collection method

All participants will be enrolled and baseline data collected on post-operative day 1–2, followed by a 10-day in-hospital Phase I cardiac rehabilitation program (post-operative day 2–11). Assessments will be performed by blinded physiotherapists at the specified time points according to the SPIRIT 2013 schedule shown in Fig. 2 (Supplementary no.3).

### Data management

Data collection and reporting will be overseen by the principal investigator and verified by an independent quality monitor. All research documentation will be cross-checked twice for accuracy. After data collection, groups will remain blinded during data entry and cleaning. The final Excel dataset will be reviewed by an allocation-blinded statistician for analysis. Data will be stored in a secure, password-protected, access-controlled server located at Datta Meghe Institute of Higher Education and Research.

Participant data will be anonymized using coded identifiers, and no personal details will appear in reports or publications. Backup copies will be maintained on encrypted drives to prevent data loss.

Participation is voluntary; participants may withdraw at any time. If consent to use existing data is denied, such data will be permanently deleted.

### Statistical methods

All statistical analyses will be performed using IBM SPSS Statistics version or equivalent software. Descriptive statistics will be used to summarize demographic and baseline characteristics, with continuous variables expressed as mean ± standard deviation and categorical variables presented as frequencies and percentages. The Shapiro–Wilk test will be applied to assess data normality. For within-group comparisons (pre- and post-intervention), the paired t-test will be used for normally distributed data, while the Wilcoxon signed-rank test will be applied for non-parametric data. Between-group comparisons (experimental versus control) will be conducted using the independent t-test for normally distributed data and the Mann–Whitney U test for non-parametric data. Analysis of covariance (ANCOVA) will be employed to adjust for any baseline differences between groups. Missing data will be addressed using an intention-to-treat approach, applying the last observation carried forward method where appropriate. In addition, subgroup analyses may be performed based on age, sex, and baseline functional capacity to explore potential secondary interactions. A p-value of <0.05 will be considered statistically significant for all analyses.

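### Pre-post tests within each arm are planned as significance tests beside the between-group test; for walking distance and strength they may well be significant with no ergometry effect.

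*Protocol article*

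**What the plan says.** The hypothesis, in the abstract's Results paragraph, compares the arms: "leg cycle ergometry, when added to conventional physiotherapy, will lead to greater improvements in scar healing, lower limb strength, functional capacity". The abstract's Objectives are comparative too.

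The Statistical methods section sets out two families of tests.
- Within each arm: "For within-group comparisons (pre- and post-intervention), the paired t-test will be used for normally distributed data". Where normality fails, a signed-rank test (Wilcoxon) takes its place.
- Between arms: "Between-group comparisons (experimental versus control) will be conducted using the independent t-test for normally distributed data", with Mann–Whitney U as the non-parametric alternative. In addition, "Analysis of covariance (ANCOVA) will be employed to adjust for any baseline differences between groups".

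One threshold covers both families: "A p-value of <0.05 will be considered statistically significant for all analyses". The abstract's Methods paragraph shortens the plan to one test of each kind, unranked: "Data will be analysed using the Mann-Whitney U test and the Wilcoxon signed-rank test; p<0.05 was deemed statistically significant".

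The Discussion says what would follow from a positive result: "If the findings confirm the hypothesized benefits, leg cycle ergometry could be incorporated as a routine component of early Phase I cardiac rehabilitation". It does not say which analysis would count as confirmation.

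**The concern.** A within-arm test takes one arm's baseline and final values as its only inputs. Its null hypothesis is no change since post-operative day 1–2, which is not the null of no difference between treatments.

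The design makes that null implausible for physical function. On day 1, Tables 1 and 2 have both groups doing supine breathing and limb exercises; by day 10 both are on a stepper. The control group receives active, progressive physiotherapy throughout. Walking distance and muscle strength can therefore be expected to rise in both arms whether or not ergometry adds anything.

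What is at stake is the reading of the results. A small p-value for change in the ergometry arm, or significance in that arm but not in the control arm, could be offered in support of routine use when the true added benefit is zero.

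**Working it through.** **1. The plan's own sample size.** Sample size calculation gives means 5.53 and 4.60, SDs 1.75 and 2.00, correlation 0.5, effect size 0.49, alpha 0.05, power 0.80, and 35 per group (42 after the dropout allowance). The formula contains Zα/2, so I take the tests as two-sided.

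- As stated, two independent means with d = 0.49: about 66 per group (67 using the t distribution). This does not reproduce 35.
- As a paired test: SD of differences = √(1.75² + 2.00² − 2 × 0.5 × 1.75 × 2.00) = √3.5625 = 1.887, and dz = (5.53 − 4.60)/1.887 = 0.493. Noncentral-t power first reaches 80% at n = 35 (79.6% at 34, 80.8% at 35). This reproduces the stated figure.
- A between-group t-test at d = 0.49 has about 52% power at 35 per arm and 60% at 42.

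The stated size thus matches a pre-post type of calculation. The sample size is a separate matter. It bears on this point because the within-arm tests are better powered than the comparison that answers the trial's question.

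**2. Chance of a significant within-arm test when ergometry adds nothing.** The documents give no recovery size, so the standardised change dz (mean change divided by SD of change) is an assumption, set equal in both arms and shown over a range. Power of the two-sided paired t-test comes from the noncentral t with n − 1 degrees of freedom and noncentrality dz√n. Critical values are 2.032 (n = 35) and 2.020 (n = 42).

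| dz | dz√n, n=35 | P(p<0.05), n=35 | dz√n, n=42 | P(p<0.05), n=42 |
|---|---|---|---|---|
| 0.2 | 1.183 | 21% | 1.296 | 24% |
| 0.3 | 1.775 | 41% | 1.944 | 48% |
| 0.5 | 2.958 | 82% | 3.240 | 89% |
| 0.8 | 4.733 | 99.6% | 5.185 | 99.9% |

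Simulating the Wilcoxon signed-rank test at n = 42 gives 47%, 88% and over 99% at dz 0.3, 0.5 and 0.8.

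**3. The between-group test under the same conditions.** With equal change in both arms, simulated rejection is 4.8–5.0% for the t-test and 4.5–5.0% for Mann–Whitney on change. The valid comparison keeps its 5% level.

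**4. Ergometry arm significant, control arm not.** With no true difference this has probability p(1 − p), where p is the within-arm probability above.

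- n = 42, dz 0.3: 0.476 × 0.524 = 0.249
- n = 42, dz 0.5: 0.886 × 0.114 = 0.101
- n = 42, dz 0.8: 0.999 × 0.001 = 0.001
- n = 35, dz 0.3: 0.407 × 0.593 = 0.241
- n = 35, dz 0.8: 0.9958 × 0.0042 = 0.004

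A two-sided 5% between-group test errs in that direction 2.5% of the time. The discordant pattern is common only at small recovery. At dz 0.8 both arms are significant in over 99% of trials.

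**The case against.** The best defence is that the protocol already plans the right analysis. Between-group tests and ANCOVA are specified, the within-group and between-group families are clearly labelled, and the hypothesis of greater improvement cannot be confirmed by a test in one arm. Adding within-arm tests changes neither the validity nor the error rate of the randomised comparison. Naming the analysis that carries the conclusion is often left to the analysis plan, which is not shown. All of this stands, and it limits the point to a risk of misreading.

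Two stronger readings are tempting. A reader might infer that the trial will judge efficacy from within-arm significance, or from significance in one arm only; no section says so, and the 25% figure is the error rate of a rule that the protocol does not adopt. A reader might also infer that the within-arm tests are bound to be significant. That depends on a recovery size that the documents do not give: at dz 0.2 the chance is only 21–24%. For the Vancouver Scar Scale, a co-primary outcome, and for PHQ-9, neither size nor direction of the expected change is stated. Nor do the two hazards coincide: the discordant pattern peaks near dz 0.3, where within-arm significance is far from certain.

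It can also be said that a within-arm confidence interval carries the same information as the p-value. That is true, so the sentence on interpretation is the more important half of the remedy.

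The defence does not remove the fact that the protocol gives significance status, at the same threshold, to tests that cannot answer its question.

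**Conclusion.** The point holds as a risk of a misleading conclusion and should be corrected. Within-arm tests are explicitly planned at p<0.05 and are not marked as descriptive. For the 6-Minute Walk Test and Manual Muscle Testing they may well be significant with no ergometry effect: from about one chance in five at a standardised change of 0.2 to near certainty at 0.8. These figures assume equal change in both arms, two-sided testing, normally distributed changes, and 35 or 42 analysed per arm. The risk is greater because the stated 35 per group reproduces as a paired calculation, while the between-group test has roughly 52–60% power at the planned effect size; a non-significant comparison beside significant within-arm results is a realistic outcome.

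**What to change.** In Statistical methods and in the abstract's Methods paragraph, drop the paired t-test and Wilcoxon signed-rank test as significance tests. Report each arm's change descriptively, as mean or median change, without p-values.

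Add a statement that any conclusion about ergometry, including the confirmation of benefit to which the Discussion refers, rests only on the between-group estimate with its 95% confidence interval. The statement should say that neither change within an arm nor a difference in significance between arms counts as evidence of a treatment effect.

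The cost is wording. No new data, patients or procedures are needed. The small downside is the loss of within-arm p-values. The change does not resolve the sample-size mismatch, which needs its own correction.
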